#### Follow up

Students will be followed at 3, 9 and 15 months past baseline, using an online evaluation questionnaire and a CO-tester supervised by research assistants. The procedure will be filled out during a school class, for an hour long session, four times during the evaluation: before the beginning of interventions in December 2013 and January 2014, at the end of the first school year in April and May 2014, at school-start in October and November 2014 and finally in April and May 2015. The same measures, questionnaires and procedure of data collection will be used during the four evaluations.

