**Methods/designs:**

This is a cluster randomized controlled trial comparing an intervention group to a control group, randomized into clusters (professional schools and classes) and stratified in three departments (Hérault, Aude and Gard) in the Languedoc-Roussillon region. The primary issue is the prevalence of daily smoking at 24 months, defined by a daily tobacco use of at least 1 cigarette, validated by CO levels in exhaled air. The primary hypothesis is that intervention will lead to decrease the daily smoking prevalence of 10% between the intervention group and the control group during a 2-year follow-up.

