### Objectives

The primary objective of this study is to measure the 24-month impact of a peer intervention based on the TPB on a highly exposed young population (from Languedoc-Roussillon vocational schools) by reaching a 10% difference in daily smoking prevalence between interventional and control groups after two-years.

Secondary objectives are to increase intention to not start smoking and/or intention to diminish tobacco consumption. This study aims to modify norms in favor of a tobacco non-consumption: behavioral norms (“I see benefits”), normative beliefs (“my parents and friend(s) would approve”), control beliefs (“I recognize the difficulties and I feel able to overcome them”), attitudes (“I am in favor to do so”), subjective norms (“I am approved by people that are important to me”) and perceived control (“I feel capable of doing this”).

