### Outcome measures

The **primary outcome measure** is the prevalence of daily smoking at 24 months defined by daily tobacco use of at least 1 cigarette validated by CO levels in exhaled air.

The **secondary outcome measures** are: using habits (tobacco, alcohol, cannabis); tobacco consumption modification characteristics (decrease, quitting); tobacco addiction and CAST score, elements of TPB (behavioral norms, normative beliefs, control beliefs, attitudes, subjective norms, and perceived control); gender; environmental quality of high schools toward tobacco.

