#### Sample size

The sample size estimation has been carried out on the basis of the literature [73, 74], with a daily smoking prevalence at 43% and a minimal absolute difference at two years between intervention and control groups equaling 10% (cf. Fig. 2). The two-sided type I error and the statistical power are fixed respectively at 5% and 80%.

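### The primary outcome is set at 24 months, but the last planned assessment falls about 15 months after baseline

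*Protocol article*

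**What the plan says.** The Outcome measures section states that the primary outcome "is the prevalence of daily smoking at 24 months defined by daily tobacco use of at least 1 cigarette validated by CO levels". The Objectives section agrees: "The primary objective of this study is to measure the 24-month impact of a peer intervention based on the TPB". The abstract places the hypothesised difference "between the intervention group and the control group during a 2-year follow-up". The Sample size section assumes "a minimal absolute difference at two years between intervention and control groups equaling 10" percentage points, and its 25% loss to follow-up is also a two-year figure. The Statistical analysis section describes the evolution of tobacco and cannabis use over two years.

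The Follow up section gives the schedule: "Students will be followed at 3, 9 and 15 months past baseline, using an online evaluation questionnaire and a CO-tester supervised by research assistants". It then dates the evaluations, which take place "four times during the evaluation: before the beginning of interventions in December 2013 and January 2014", next in April–May 2014, next in October–November 2014, and for the last time in April–May 2015. The same measures and procedure apply at all four.

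**The concern.** The end-point definition and the data-collection plan cannot both be followed. The article does not merely leave the 24-month visit undescribed. It gives a closed, dated list of four evaluations, and none is near 24 months.

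The planned mixed model includes a group-by-time-point interaction, so the primary contrast should be read at the primary time point. That time point is not among the observed ones. The analyst would have to report the last contrast under a 24-month label, or use the random-slope model to project past the last observation. Neither tests the stated primary hypothesis with observed data. Readers and evidence synthesisers could then credit the trial with a two-year effect that was not observed. Durability matters here, because the Background section itself says that solid evidence on the long-term effects of peer education has been lacking.

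**Working it through.** **1. Inputs**

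| Item | Value | Section |
|---|---|---|
| Primary time point | 24 months | Outcome measures; Objectives; abstract |
| Planned follow-up | 3, 9 and 15 months after baseline | Follow up |
| Baseline window | December 2013–January 2014 | Follow up |
| Final evaluation window | April–May 2015 | Follow up |
| Effect and horizon | 43% daily smoking, 10-point absolute difference, two years | Sample size |
| Loss and horizon | 25%, two years | Sample size |

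**2. Elapsed time to the last evaluation**

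Months = days / 30.4375, with each window taken from the first day of its first month to the last day of its second month.

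- Shortest: 31 January 2014 to 1 April 2015 = 425 days; 425 / 30.4375 = 14.0 months.
- Longest: 1 December 2013 to 31 May 2015 = 546 days; 546 / 30.4375 = 17.9 months.

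The shortfall against 24 months is 24 − 17.9 = 6.1 to 24 − 14.0 = 10.0 months. Against the nominal 15 months it is 9 months. Twenty-four months after the baseline window would be December 2015–January 2016.

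The same calculation puts the second evaluation at 2.0 to 5.9 months and the third at 8.0 to 12.0 months. The nominal labels of 3, 9 and 15 months therefore all fit the calendar, so 15 is not a misprint for 24.

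**3. Is the sample size tied to the two-year horizon?**

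The plan's own figures reproduce:

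- Unadjusted: two proportions, 0.43 against 0.33, two-sided α = 0.05, power 0.80, 1:1 allocation assumed, no continuity correction. n per arm = [1.960√(2 × 0.38 × 0.62) + 0.842√(0.43 × 0.57 + 0.33 × 0.67)]² / 0.10² = 369, or 738 in total (stated 740).
- Inflation: cv = 4.9 / 20 = 0.245; 1 + (20(1 + 0.245²) − 1) × 0.1 = 3.020; 740 × 3.020 = 2235 (stated 2240).
- Loss: 2240 / 0.75 = 2987 (stated 3000).

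The arithmetic is sound, but the 10-point effect and the 25% loss are both stated for two years. The article gives neither figure for 15 months, so it cannot be said whether the required number would rise or fall at that horizon.

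**4. Order of registration and last evaluation**

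The article reports retrospective registration on 11/12/2015. Whether the day or the month comes first, that date is after May 2015.

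**The case against.** The strongest reply is that the programme runs by school year. The article refers to the end of the first school year, to an event closing each school year, and to interviews at the end of the first and second years. The final evaluation comes near the end of the second school year, so the two-year wording could loosely mean two school years. CO-checked daily smoking is also collected at that evaluation by the same procedure, so the outcome variable exists and only its time point is wrong. Finally, no change in the sample size has been shown.

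Most of this stands as a limit on the point. The trial is not without a usable smoking outcome, the two-year phrases alone might be reconciled with the schedule, and no sample-size error is claimed. The reply does not rescue the outcome definition. The abstract, Objectives and Outcome measures all specify 24 months, while the Follow up section counts months from baseline and stops at 15. If two school years were meant, the wording of the primary outcome is wrong and needs the correction below.

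A further fair objection is that moving a primary time point after the last evaluation date is a change to the outcome definition, and more than tidying. That is why the fix includes disclosure.

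**Conclusion.** The point holds and must be fixed. As defined, the primary outcome has no planned measurement. The last evaluation is nominally 15 months after baseline, and 14.0 to 17.9 months by the stated windows, leaving a gap of 6.1 to 10.0 months. No combination of the stated dates reaches 24 months. A full protocol or analysis plan that is not shown would not remove the conflict, because the article itself fixes both the time point and the dated list of evaluations.

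The conclusion rests only on the article's dates and on reading its list of four evaluations as complete. It does not depend on any assumed effect, attrition or correlation. The consequence for power is unknown.

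**What to change.** Redefine the primary outcome as CO-validated daily smoking at the final evaluation in April–May 2015, nominally 15 months after baseline and at the end of the second school year. Carry this through the abstract, primary hypothesis, Objectives, Outcome measures, Sample size and Statistical analysis sections. Change Fig. 2 too if it shows a two-year axis or label; the figure was not available, but the Sample size section cites it for the two-year difference. State whether the 10-point difference and the 25% loss are still assumed at that horizon. Say openly that registration came after the final evaluation, and give the date of and reason for the change of time point.

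The cost is an amendment to the text and a dated disclosure, with no new data. The conclusion then concerns about 15 months and not two years.

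If 24 months is truly the target, the alternative is a fifth evaluation around December 2015–January 2016, made primary. That needs another round of school visits, in a third school year, and its feasibility cannot be judged from the article.

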#### Sample size

The sample size estimation has been carried out on the basis of the literature [73, 74], with a daily smoking prevalence at 43% and a minimal absolute difference at two years between intervention and control groups equaling 10% (cf. Fig. 2). The two-sided type I error and the statistical power are fixed respectively at 5% and 80%.

**Fig. 2 Fig2:**
[figure not shown]
Expected 10% difference in daily smoking prevalence between interventional and control groups

To take into account the impact of cluster randomization, sample size will be multiplied by the variance inflation factor: 1 + (m(1 + cv^2^)-1)ρ with m the mean number of subjects per cluster, cv the coefficient of variation equal to ratio between the standard deviation of the cluster sizes and m, and ρ the intra-class correlation coefficient, which can be seen as the measure of the cluster effect.

If it seems appropriate to randomize the schools in order to avoid highly important contamination bias for the classes of one same school, it also seems essential to consider intra-class correlation, which is surely more important than intra-school correlation itself. In view of numerous studies where randomization is carried out according to this principle, ρ is fixed between 0.10 and 0.20.

Therefore, 740 participants are required according to the previous assumptions, without taking into account cluster effect. Considering mean of students per class around 20 (standard deviation of 4.9) and an ICC equaling 0.1, 2240 participants are required. Considering a lost to follow-up rate at two years around 25% and between and within school variability greater than previous assumptions, it seems reasonable to include 3000 participants for this study, which corresponds to around 125 classes and 14 schools.

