## Methods/design

### Study design

This is a cluster randomized controlled trial. The intervention group will be compared to the control group after randomization into clusters (professional schools and classes) stratified in three departments of France (*Hérault*, *Aude* and *Gard*). The intervention will be a smoking prevention program made by the peers, based on the Theory of Planned Behavior (TPB).

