### Randomization

The trial will be randomized into clusters (vocational high school) and stratified in three departments of France (Hérault, Aude and the Gard). As the study will be carried out throughout several departments where smoking consumption levels and socio-demographic parameters differ, the randomization will be stratified by department. The risk of interpenetration (or contamination) between schools will be minimized by retaining vocational high schools from different geographic areas. The classes from the same school will not included in two different randomization groups.

Randomization by random blocks will be performed using Stata software (version 13, StataCorp, College Station, US) by an independent statistician and considering stratification according to area of the region (department) and size of school (in terms of number of children per school).

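### Schools are randomised, but the sample size is inflated only for clustering within classes of 20, so the stated 80% power does not follow from 14 schools

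*Protocol article*

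**What the plan says.** - **Unit of randomisation.** The Randomization section says "The trial will be randomized into clusters (vocational high school) and stratified in three departments of France", and adds "The classes from the same school will not included in two different randomization groups". The school is therefore the randomised cluster. The Study design section, like the Abstract, puts it differently: "after randomization into clusters (professional schools and classes").
- **Target.** The Sample size section works "with a daily smoking prevalence at 43% and a minimal absolute difference at two years between intervention and control groups equaling 10" points, and "The two-sided type I error and the statistical power are fixed respectively at 5% and 80"%.
- **Inflation.** The factor is 1 + (m(1 + cv²) − 1)ρ, with m defined as the mean number of subjects in a cluster. The value put in is the class size: "Considering mean of students per class around 20 (standard deviation of 4.9) and an ICC equaling 0.1, 2240 participants are required".
- **Reason given.** Having accepted that schools should be randomised to avoid contamination, the section argues that "it also seems essential to consider intra-class correlation, which is surely more important than intra-school correlation itself". No school-level ICC and no school size is used.
- **Final number.** 3000 pupils, about 125 classes and 14 schools. The rise from 2240 is attributed to 25% loss to follow-up and to more variability between and within schools than had been assumed.
- **Analysis.** The Statistical analysis section fits random effects for both schools and classes.

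**The concern.** The inflation factor has to describe the group of pupils that receives one allocation. Here that is the school, with about nine classes in it. Using m = 20 would be right if each class were randomised independently, which the Randomization section rules out.

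That the class ICC exceeds the school ICC does not justify leaving the school out. The two contributions add. The class term is multiplied by about 20 classmates, the school term by about 140 schoolmates in other classes, so a school ICC a fraction the size of the class ICC can dominate.

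The 80% power for 43% versus 33% supports the interpretation of the primary result. If true power is clearly lower, a non-significant result could be taken as evidence against a 10-point effect when the trial had too few schools to show one.

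**Working it through.** **1. Reproducing the plan's figures**

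Inputs from the Sample size section: 43% versus 33%, two-sided α 0.05, power 80%. Allocation is taken as 1:1 (not stated, but it reproduces 740).

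- Per arm: n = [1.96√(2 × 0.38 × 0.62) + 0.8416√(0.43 × 0.57 + 0.33 × 0.67)]² / 0.10² = 368.7, so 369 per arm and 738 in total (stated: 740).
- cv = 4.9/20 = 0.245, so 20(1 + cv²) = 21.2.
- Design effect = 1 + (21.2 − 1) × 0.10 = 3.02.
- 740 × 3.02 = 2235 (stated: 2240).
- 2240/0.75 = 2987 (stated: 3000).

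The arithmetic is sound and confirms that only class-level clustering was used. Dropout uses all but 3000 − 2987 = 13 of the pupils, so the stated allowance for extra school variability is in effect nil.

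**2. Design effect with the school as the cluster**

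Let ρ_class be the correlation between classmates and ρ_school the correlation between pupils of the same school in different classes:

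DEFF = 1 + (m_class(1 + cv²) − 1)ρ_class + (m_school − m_class(1 + cv²))ρ_school

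The plan's 3.02 is this expression with ρ_school = 0.

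Inputs: 3000 × 0.75 = 2250 evaluable; 2250/14 = 160.7 per school; ρ_class = 0.10. Evaluable class size is taken as 18 (2250/125) to 20 (the plan's m). School sizes are treated as equal, which is favourable to the plan. **ρ_school is an assumption; the article gives no value.**

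**3. Power**

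With n = (2250/DEFF)/2 per arm, power = Φ{[0.10 − 1.96√(2 × 0.38 × 0.62/n)] / √[(0.43 × 0.57 + 0.33 × 0.67)/n]}. Example at ρ_school = 0.01 and 20 per class: DEFF = 3.02 + 139.5 × 0.01 = 4.42; effective N = 2250/4.42 ≈ 510; n = 255; power = Φ[(0.1 − 0.0843)/0.0428] = 64%.

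The t column is a sensitivity version using the noncentral t on 14 − 2 = 12 degrees of freedom. Ranges cover 20 down to 18 evaluable pupils per class.

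| ρ_school | DEFF (20 per class) | Power, normal | Power, t on 12 df |
|---|---|---|---|
| 0 | 3.02 | 80–83% | 74–77% |
| 0.005 | 3.72 | 72–74% | 65–67% |
| 0.01 | 4.42 | 64–66% | 57–59% |
| 0.02 | 5.81 | 53–54% | 47–48% |
| 0.05 | 10.00 | 34% | 30% |

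**4. Break-even and detectable difference**

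- With ρ_class = 0.10, normal-theory power falls below 80% once ρ_school exceeds about 0.0002 (20 per class) or 0.002 (18 per class).
- With no separate class effect, DEFF = 1 + (161 − 1)ρ_school, and 3.02 is enough only up to ρ_school = 2.02/160 ≈ 0.013.
- The plan's own formula with the school as cluster, equal sizes and ρ = 0.10 gives 1 + 159.7 × 0.10 = 17.0, and power of about 22%.
- The difference detectable with 80% power (12 df) is about 13 points at ρ_school 0.01 and 15 points at 0.02.

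**The case against.** **The numbers are computed correctly.** True: 740, 2240 and 3000 all follow from the inputs. The fault is the level at which the formula is applied.

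**The size of the loss is not in the document.** This also stands. The school ICC range is assumed, and at 0.005 the shortfall is moderate. That 80% is not supported unless the school ICC is near zero does not depend on the choice of range.

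**The planned analysis is not an unadjusted comparison.** This is the strongest point. The model adjusts for initial consumption and school characteristics and uses repeated measurements, and randomisation is stratified by department and school size; all of this can reduce between-school variance. Under the working above (18 per class, normal theory), 80% power returns if about 87% of the variance remains at school ICC 0.005, 72% at 0.01 or 54% at 0.02; at 0.05 only about 31% could remain. Part of the loss may therefore be recovered. But the Sample size section takes no credit for adjustment and gives no baseline–outcome correlation from which to claim it.

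**The t reference is a choice.** The article names no small-sample method, so those results are a sensitivity analysis. The normal-theory results alone carry the point.

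**Extra school variability was allowed for.** The sentence is there, but it amounts to 13 pupils.

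**The test remains valid.** Agreed: a school random effect puts school variance into the standard error, and a wide confidence interval would itself be a warning. The defect is in planned precision and the power claim, not in the primary test.

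**Conclusion.** The concern holds. The trial randomises schools, the power calculation treats classes as if they were randomised independently, and the allowance said to cover school variability is used up by dropout. With 2250 evaluable pupils in 14 equal schools, class ICC 0.10 and no credit for covariate adjustment, normal-theory power is 72–74% to 34% over assumed school ICCs of 0.005 to 0.05, and 65–67% to 30% with 12 degrees of freedom. The exact loss depends on a school ICC that the article does not give and on how much the adjusted model recovers. The mismatch between design and calculation depends on neither. The naming of both schools and classes as randomised clusters in the Abstract and Study design contradicts the Randomization section and should be corrected with it.

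**What to change.** 1. Rewrite the sample size paragraph with the school as the cluster, using the three-level design effect above and 12 degrees of freedom for 14 schools.
2. Replace the 80% claim by the power, or the detectable difference, that 14 schools and 3000 pupils give over a stated range of school ICCs, for example 0.005 to 0.05. If credit is taken for baseline adjustment, state the assumed correlation and show its effect.
3. Either drop the remark about greater school variability or give it a number.
4. In the Abstract and Study design, name schools alone as the randomised clusters.

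The cost is rewording and a less favourable power figure; no extra pupils are needed. Spreading the same pupils over the 20 schools to be approached would raise normal-theory power at school ICC 0.02 from 53–54% to 60–62%. But the article's calendar ends in spring 2015, before the December 2015 registration, so that change is probably no longer open, and the restatement is what matters.

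### The 3000 is said to cover 25% loss and extra clustering, but on the plan's own calculation loss uses it up, and 3000, 20 per class and 125 classes do not agree

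*Protocol article*

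**What the plan says.** The Sample size section of the protocol article (continuing below Figure 2) assumes 43% daily smoking, a 10-point absolute difference at two years, two-sided 5% error and 80% power. From these it states that "740 participants are required according to the previous assumptions, without taking into account cluster effect".

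For clustering, "sample size will be multiplied by the variance inflation factor: 1 + (m(1 + cv^2^)-1)ρ", where m is mean cluster size and cv its coefficient of variation. On the intra-class correlation it says "ρ is fixed between 0.10 and 0.20". It then works one case only: about 20 students per class, SD 4.9, ICC 0.1, giving 2240.

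The last step names two allowances together: about 25% loss at two years, and "between and within school variability greater than previous assumptions". On that basis "it seems reasonable to include 3000 participants for this study, which corresponds to around 125 classes and 14 schools".

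**The concern.** The closing sentence tells the reader that 3000 absorbs attrition and also leaves room for stronger clustering than the 0.10 used. That matters because 0.10 is the favourable end of the article's own range. If the room is not there, power falls below the fixed 80% over much of that range, and a reader would wrongly take the design as robust to clustering.

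The sentence also gives recruitment in two units, students and classes, that do not match the stated class size. Class size enters the inflation factor directly, so the mismatch affects the required total as well as the logistics.

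**Working it through.** **Inputs (all from Sample size).** 43% vs 33%; α = 0.05 two-sided; power 80%; m = 20, SD 4.9, so cv = 4.9/20 = 0.245; ICC ρ = 0.10, declared range 0.10 to 0.20; loss 25%; total 3000; 125 classes. Assumption: 1:1 allocation, which is not stated but reproduces 740.

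**1. Reproduce the plan's figures.**
- Unclustered, pooled variance: n per arm = [1.96·√(2·0.38·0.62) + 0.8416·√(0.43·0.57 + 0.33·0.67)]² / 0.10² = 369, so 738 in total (stated 740).
- Inflation factor: 1 + (20·(1 + 0.245²) − 1)·0.10 = 3.02.
- 740 × 3.02 = 2235 (stated 2240).

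Both stated figures hold.

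**2. The loss step.** 2240/(1 − 0.25) = 2987, and 3000 − 2987 = 13 enrolled students. In followed students, 3000 × 0.75 = 2250 against 2240, so 10 to spare.

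**3. Largest ICC that 2250 followed students support.** Solve 740·[1 + (m(1 + cv²) − 1)ρ] = 2250, so ρ = (2250/740 − 1)/(m(1 + cv²) − 1). With m = 20: 2.0405/20.2005 = 0.101.

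The article does not say whether 20 is enrolled or followed, so I repeated this with the followed class size after individual loss: 20 × 0.75 = 15, and 24 × 0.75 = 18.

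**4. Power with 2250 followed.** Effective n per arm = 2250/(2 × factor). Power = Φ{[0.10 − 1.96·√(2·0.38·0.62/n)] / √[(0.43·0.57 + 0.33·0.67)/n]}. In the table, cv is held at 0.245.

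| Followed per class | Factor at ICC 0.10 / 0.15 / 0.20 | Power | Enrolment needed for 80% | Largest ICC supported |
|---|---|---|---|---|
| 20 (as the article computes) | 3.02 / 4.03 / 5.04 | 80% / 68% / 59% | 2980 / 3976 / 4973 | 0.101 |
| 15 (20 enrolled) | 2.49 / 3.24 / 3.98 | 87% / 78% / 69% | 2457 / 3192 / 3927 | 0.137 |
| 18 (24 enrolled) | 2.81 / 3.71 / 4.62 | 83% / 72% / 62% | 2771 / 3663 / 4554 | 0.113 |

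Holding SD at 4.9 instead of cv lowers the last two ICC limits to 0.131 and 0.111. In every row, the enrolment needed at ICC 0.15 exceeds 3000.

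**5. Class count.** 125 × 20 = 2500; 3000/20 = 150; 3000/125 = 24.

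**The case against.** The best defence is that loss also shrinks classes. If 20 is the enrolled size, the factor at ICC 0.10 is 2.49, the requirement is 740 × 2.49 = 1843 followed or 2457 enrolled, and about 540 of the 3000 are genuine margin. This stands as a possible reading. The margin is therefore nil on the article's own calculation but modest on this one, and a reader who inferred that 3000 has no slack on any reading would go too far. Even so, the margin ends near ICC 0.13 to 0.14.

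Other stronger inferences are also unsupported:
- *That 125 classes of 20 would miss the requirement, with 73% power.* The 73% puts 1875 followed students in classes of 20, which holds only if whole classes are lost. With individual loss there are 15 per class. The requirement is then 1843 (cv held) to 1894 (SD held), and power is about 80 to 81%.
- *That 125 classes of 24 would require 2516 followed and 3355 enrolled.* This uses 24 followed per class (factor 3.40) and then divides by 0.75, which again describes whole-class loss. With 18 followed, 3000 exceeds the 2771 to 2796 needed at ICC 0.10. The Statistical analysis section allows for missing schools, classes and children, so whole-class loss is possible, but the sample size text gives only a general loss rate.
- *That the class count is the wrong figure.* Class size and class count are both given as approximate, and 24 lies within one SD of 20. The document cannot settle which figure to change. Approximation does not, however, cover a 20% gap in a quantity that drives the inflation factor.

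Could the spare 200 from 2240 × 1.25 = 2800 be the margin? No: 2800 × 0.75 = 2100, which is below 2240.

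**Conclusion.** The concern holds in a bounded form. The 740 and 2240 are sound; the fault lies in the final sentence. On the article's own method, 3000 covers 25% loss at a class ICC of about 0.10 and almost nothing more (13 enrolled students, supported ICC 0.101). On the kinder readings of class size the supported ICC rises to about 0.11 or to 0.13–0.14. None reaches 80% power at 0.15 or 0.20, where power is 68–78% and 59–69% across the three readings. The total, the class size and the class count are mutually inconsistent whichever reading is taken.

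This rests on 1:1 allocation, the article's inflation formula with class as the cluster, and exactly 25% loss. No separate school-level term is included, although schools are the randomized unit. Any additional correlation between classes of the same school would lower these power figures.

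**What to change.** 1. Reconcile the three figures: about 150 classes at 20 per class, or 125 classes at 24. State whether the class size is enrolled or followed.
2. Delete the claim that 3000 also covers greater variability, or quantify it. As computed, the text should say that 3000 covers 25% loss at a class ICC of about 0.10.
3. Report power with 2250 followed at ICC 0.10, 0.15 and 0.20, using the row that matches the reconciled class size: about 80%, 68% and 59% with m = 20 as now computed; about 87%, 78% and 69% with 15 followed per class; or about 83%, 72% and 62% with 24 enrolled and 18 followed.
4. If whole-class loss is considered plausible, give 2516 followed / 3355 enrolled (125 classes of 24) or 73% power (125 classes of 20) as a labelled sensitivity case, not as the base requirement.
5. Say that the figures exclude a school-level term.

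The cost is a few figures in one paragraph and a less favourable statement of power. Enrolment need change only if the authors want to keep a claim of robustness at ICC 0.15 or above.
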